## **4. Selection and withdrawal of participants**

### **4.1 Inclusion criteria**

Expectant pregnant women and their partners  
≥ 18 years old  
Singleton pregnancy  
Due to give birth at Hvidovre Hospital.  
Able to speak and understand Danish  
Being legally able and willing to provide signed consent

### **4.2 Exclusion criteria**

Not providing signed informed consent

### **4.3 Participant withdrawal**

Participants are free to withdraw entirely from the Newborn trial at any time, and this will not have consequences for the participant's further treatment. When possible, participants will be asked if they will allow their already collected data to be used in a database, and/or publication.

## **5. Experimental interventions**

A detailed intervention manual will be created for the trial facilitators. The following subjects will be covered in the sessions:

The NEWBORN programme includes short verbal presentations from the group facilitator, individual exercises, short film presentations, time for discussions and reflection. Parents are given homework in the form of minor exercises in preparation to each session. Educational subjects are: the transition to

parenthood; couple communication; birth; breastfeeding; and taking care of a newborn. A patient-network website has been created as a supplement to the sessions. The programme is focused on parenting resources important to the birth process, parenting and mental health, and that appear amenable to change, i.e.: social support, parenting alliance and communication with partner, cognitive coping, e.g., self-efficacy and parenting skills. These elements have been addressed in the following manner:

- I. Social support: formal and informal, emotional, informational and instrumental. Groups of 6-8 couples are offered three times 2.5 hour sessions during pregnancy and one session five weeks post-partum. The groups are composited to enable participants establish relations with other expectant parents in their local area. Sessions are led by a midwife and the postnatal session will include a health visitor. A patient-network website enables parents to gain further information, communicate with other parents and consult online with a midwife and a health visitor.
- II. Parenting alliance: adding a component supporting the couples in the transition to parenthood and couple communication.
- III. Cognitive coping: embedding sources of self-efficacy into programme content and delivery, and by creating an environment which enables parents to discuss feelings and concerns, enhances their awareness of own resources, problem-solving strategies, and future challenges in parenting and emotional regulation
- IV. Parenting skills: increasing information and exercises with feedback, e.g., on recognising signs and symptoms of thriving in the newborn, couple communication etc.

In short, the approach aims at strengthening relationships and improving information and problem solving skills for expectant parents in order to ease birth and the transition to parenthood.

To maximise the potential for population uptake classes have been established at three local midwifery sites. A comprehensive guide and education material for course facilitators has been developed, and facilitators, i.e. midwives and health visitors are trained at one-day workshops. The framework for the classes is based on an estimate of adequate time allocated to each subject, and what service providers deem a sustainable service.

Session 1 (approximately 25 weeks gestation):

- The transition to parenthood – new roles and responsibilities, emotional adjustment
- Common changes and challenges in the relationship during and after pregnancy
- Couple communication

- Meaning of own childhood when becoming parents

During the first session the parents are introduced to one another and to the scope and outline of the entire programme. The midwife invites the parents to think about and since discuss their expectations of the greatest joys and greatest challenges of parenthood. Afterwards the midwife informs the parents about common changes and challenges in the relationship during pregnancy and after birth, and the importance of good communication. A short film is shown teaching the parents about good communication skills. The film is developed by the Danish Centre of Family Development and is inspired by PREP (36). The film is followed by practical couple-communication exercises. Women attending the classes alone either pair up or conduct the exercise with the midwife. In short the exercise entails one person listening actively and without interrupting while the other person describes thoughts and feelings about a certain topic. Afterwards the person listening is encouraged to acknowledge what she/he has heard before changing roles. This communication exercise is used throughout the entire programme covering different topics e.g. expectations of parenthood, labour, the relationship after birth etc. The aim is to try to understand the other person's perspective before trying to be understood. The importance of one's own childhood when becoming a parent is also a topic in this session (35). Participants are asked to think back to their own childhood, how they were raised, their parents' parenting style (e.g. warm and affectionate, strict etc), traditions etc. Afterwards they are to consider things they would like to carry forward into their own parenting as well as things they might want to do differently. Finally the couple begin to discuss the topic using the communication technique they have been taught. The aim is to start a thought process. As there is not sufficient time for long in depth discussions participants are encouraged to carry on the discussions at home. During the first break participants who wish to do so are asked to write down their contact details so that they can be shared in the group. Throughout all the sessions the midwife has a facilitating role helping discussions along if needed and commenting where appropriate. At the end of all sessions participants are asked to consider and write down the most important take home points of the session.

Suggested preparation for the next session: seven short informational film clips (duration between 2 and 7 minutes) on the first signs of labour, the time at home in early labour, birth, when there is a need for obstetric intervention, and pain relief.

The films, exercises, and written information on session topics are available on the network website.

Session 2 (approximately 33 weeks gestation):

- Expectations in relation to birth
-

- The normal course of labour
- When there is a need to intervene in labour
- Pain relief and coping strategies
- Partner support during labour

The aim of this session is providing the participants with information, and enhancing their existing knowledge and understanding of the normal course of labour, pain-relief, and what might be expected if there is a need for obstetric intervention. After a short verbal presentation by the midwife the couples discuss their hopes and expectations for labour and birth using the communication framework - they are asked to consider their individual resources and action competencies in relation to increasing the likelihood of obtaining their wishes. Also the couples are asked to discuss how they might support one another during birth and labour – using practical examples. For the topic on pain relief the women are first asked to discuss their thoughts and previous experiences with coping with pain and physical and mental strain – what did they do, what helped them, can they use any of these strategies during labour? Next they discuss their thoughts and knowledge on various methods of pain relief. Meanwhile the men discuss their thoughts and feelings about their role during labour and birth. Plenary discussions and summing up thoughts and ideas are used so that participants can learn from and be inspired by one another. Vicarious learning and feedback are considered important in relation to self-efficacy (20).

Suggested preparation for the next session: participants are encouraged to ask women in their social network about their breastfeeding experiences, and read a pamphlet that is handed out on breastfeeding (37).

Session 3 (approximately 35 weeks gestation):

- Feeding a newborn –including breastfeeding intention, expectations, facts and myths
- Interpreting the newborn's signs, symptoms and behaviour
- Taking care of a newborn – baby cues, bonding, and practical issues
- Mood swings and postnatal depressive symptomatology

Participants discuss wishes for feeding their newborn and feeding experiences in their networks in small groups. The midwife then talks about how expectations, support, and the advice received from family and friends may affect e.g. breastfeeding intention and perseverance in the case of difficulties. Bearing the breastfeeding experiences of individuals in their social networks in mind (preparation for this session), participants are encouraged to consider who it might be most helpful to seek breastfeeding support and advice from if necessary.

Cards with a variety of breastfeeding topics are spread out on the table, and participants are asked to pick a topic that they wish to hear more about, and tell the group why they have picked the chosen topic. Topics include e.g. how to tell that the baby is getting enough milk, positioning, importance of partner support, feeding patterns, breast engorgement etc. There are certain topics that the midwife is told to cover regardless of whether it has been picked by a participant or not e.g. how to tell the baby is getting enough milk. The pilot study showed that participants are likely to choose a topic they already know something about in order to receive verification and feedback from the midwife and from the other participants (unpublished data) – this may help increase self-efficacy.

The midwife gives information and shows short film clips on baby cues and sleep patterns. The importance of communicating with the newborn is underlined. Information on the prevention of cot death is given. Next the initial time at home with a newborn and the importance of social networks for emotional and practical support is discussed (the group is considered a potential supportive social network). Participants are given an exercise where they are asked to fill in a list of expected daily activities after the baby is born. Afterwards they compare their list with their partner's or that of another group member before summing up in plenum. The aim of this exercise is to increase awareness of what changes life with a newborn has on a daily routine, how much time is spent on breastfeeding etc. (35). Participants are also asked to consider activities that give them energy and pleasure (e.g. playing football, going out with friends, reading a book), and how they might incorporate some of these activities in their new daily lives (35). Next participants are encouraged to reflect upon how they normally handle worries, and to discuss this topic with their partner. Finally common emotional reactions and postnatal depressive symptomatology is covered. The importance of being open about these emotions and supportive of one another is stressed, as is the importance of seeking help when deemed necessary.

Session 4 (approximately 5 weeks post-partum):

- Birth experiences
- Mood swings and postnatal depressive symptomatology
- The first time at home with a newborn – experiences, challenges and solutions
- Couplehood – partner support, communication, division of household tasks

This session is carried out by a midwife as well as a healthcare visitor. The aim is for the newborn parents to share birth experiences, and their experiences in their new roles as parents so far. The topic of common emotions and postnatal depressive symptomatology is revisited. Next groups of four are asked to discuss how being a parent is different to what they expected, which challenges they consider to be the greatest, how they cope with/handle these challenges, and what have been the greatest joys. The parents are able to ask the midwife and the healthcare visitor practical questions during the break.

---

After the break, using the communication framework, couples are asked to discuss what the best change has been in their partner after becoming a parent, what has worked really well in the relationship, and in sharing household tasks, and what could make it even better. Finally the healthcare visitor talks about sex (including contraception) and intimacy after becoming parents.

### **5.1 Concomitant medication/treatment**

All participants are free to make use of concomitant antenatal/postnatal services and parent groups. As use of other services and parent groups may influence the outcomes that we are interested in, use and services will be examined, documented and given careful consideration in the analyses.

### **5.2 Monitoring for participant compliance**

We will evaluate whether the protocol is followed in program delivery, how much of the intended program the participants are receiving, as well as what proportions of the intended groups are participating in the program. Furthermore we will monitor use of the website.

## **6. Assessment of outcome measures**

### **6.1 Efficacy variables**

Data will be collected via the hospital obstetric database, the national registers, and web-based questionnaires and collected in an electronic case record form (eCRF) at: baseline i.e. time point 0 (tp0) (<20 weeks gestation), 37 weeks gestation (tp1), 9 weeks (tp2), 6 months (tp3) and 1 year after expected due date (tp4).

The primary outcome is:

Epidural use during labour – data from the hospital obstetric database (tp2)

Secondary outcomes are:

Stress – perceived stress, parenting stress - questionnaire data (tp0,2,3,4)

Parenting alliance – questionnaire data (tp2,3,4)

Explorative outcomes:

Antenatal and Post-natal depressive symptomatology and anxiety – questionnaire data (tp0,1,2,3)

Breastfeeding - questionnaire data (tp0,1,2,3)

Use of healthcare services i.e.: for the parents obstetric intervention i.e. augmentation of labour, vacuum extraction, caesarean rate - data from the hospital obstetric database (tp2), and contact to

healthcare professionals for depressive symptomatology and anxiety, and unscheduled postnatal visits—questionnaire data (tp2,3). For the child i.e. neonatal readmissions to hospital, contacts to accident and emergency departments (A & E), GP and doctor on call during the child's first year of life (composite measure). Also use of the regional emergency phone line – data from the national registers (tp4).

Mental well-being – questionnaire data (tp 1,2,3)

Family medicine use – questionnaire data (tp2,3) and register data (tp4)

Smoking - questionnaire data (tp 1, 2)

Satisfaction with relationship and family break-ups - questionnaire data (tp 0,2,3), and data from the national registers on divorce and break-ups (tp4)

In this trial the intermediate outcomes of interest are:

Parenting resources: Trust in own ability to cope with/self-efficacy: 1) birth (tp1), 2) discharge (tp1) 3) parenting (tp2,4) breastfeeding (tp0,1); couple communication (tp0,1,2,3); social support/network (tp0,1,2,3)

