### **3.5 Duration**

Participants will be invited to participate in the trial at their first antenatal visit. The intervention consists of 4 sessions that last for 2,5 hours per session. The first intervention session will take place at 25 weeks gestation, followed by 2 sessions at 33 and 35 weeks of gestation, and a post-natal session 5 weeks after expected due date.

The control group are offered two lectures in an auditorium during pregnancy.

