#### *Antenatal and postnatal depressive symptomatology and anxiety*

In order to identify mothers (and fathers) with a possible emerging antenatal or postnatal depression, we will use the 10-item Edinburgh Postnatal Depression Scale (EPDS) (tp 0,1,2), and the Major Depression Inventory (MDI) (ICD-10) (tp 3). The EPDS is currently believed to be the best non-comprehensive screening tool, despite its relatively low predictive value and has recently been evaluated in a Danish population (57). The MDI is used to increase the diagnostic specificity and has similarly been used in a Danish population. The Hopkins Symptom Check List (SCL-25) first 10 items (anxiety score, SCL-anxiety) will be used to measure anxiety (tp 1,2,3).

An estimated 7% of expectant mothers suffer from depressive symptoms during the first trimester of pregnancy, increasing to 12-13% during the third trimester and 3 months postpartum (58, 59). Depression is associated with a high risk of anxiety, poor self-care, partner relationship problems (60), fear of childbirth (61), and poor obstetric outcomes (62). Furthermore maternal depression is associated with impaired mother-infant relations (63), an increased risk of feeding and growth problems (64), and regulatory and emotional problems (65-71) in the child.

The Newborn trial aims to address some of the risk factors associated with AND and PND e.g. self-efficacy, stress and social support (72, 73) which may reduce the occurrence. However, depression is a complex phenomenon with many pathways. As PND may have negative long-term consequences - especially if left untreated - how to recognize signs and symptoms of PND and how to act on these symptoms (e.g. contacting the general practitioner) is included as an important topic in the Newborn trial. It is therefore possible that a larger proportion of the intervention group will report and seek help for AND and PND.

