#### *Medicine use*

Family medicine use will be recorded by use of questions from the Danish National Health survey program (tp2,3,4) (80). Some medicine is sensitive to psychosocial circumstances and may reflect a general strategy for coping with daily stressors (81-83). A high level of perceived stress is associated with use of over-the-counter medicine, primarily analgesics (82-84). Depression is also associated with excessive analgesic use (84). Administration of over the counter medications, especially analgesics, for children is common (85). Not all medicine use among children can be explained by prevalence of symptoms (85). Qualitative studies suggest that some medicine administration may be a form of "social medication," to give parents control over children's behavior that they perceive as fractious and irritating (86)

Smoking is associated with stress and will be measured by questions from the national health interview surveys.

Mental well-being: Mental health promotion and wellbeing strategies are urgent public health concerns and the need for the promotion of mental health and wellbeing has now become a feature of government policy within many countries throughout the world. It is possible that the Newborn intervention may increase mental wellbeing. It will be measured using the Warwick-Edinburgh mental well-being Scale (WEMWBS) (tp 1,2,3,4).

Intermediate measures:

When evaluating health promoting programs a number of intermediate indicators (e.g. self-efficacy, beliefs, knowledge, skills acquisition) should be used to assess various components of a program and to allow illuminative evaluation (87).

Furthermore for some particular health promotion models, intermediate indicators will serve as outcome indicators (87). For example, while evidence of self-efficacy might provide an intermediate indicator of ultimate success in terms of a reduction in risk factors for a negative outcome, self-efficacy might equally be judged as a desirable outcome in its own right for a salutogenic model of health promotion.

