| Smoking question from the National health interview survey      | Smoking                                                                               | • 1,2,3,4   |
| Mental Well-being                                               | The Warwick-Edinburgh Mental Well-being Scale                                         | • 1,2,3,4   |
| Intermediate measures                                           |                                                                                       |             |

| Tools                                                             | Outcomes                                                                    | Time points |
|-------------------------------------------------------------------|-----------------------------------------------------------------------------|-------------|
| Single item questions                                             | Trust in own ability to cope with birth                                     | • 1         |
| Single item questions                                             | Trust in own ability to cope at discharge                                   | • 1         |
| Two single item questions                                         | Trust in own ability to breastfeed                                          | • 0,1       |
| Scale from ALSPAC                                                 | Communication in the relationship                                           | • 0,1,2,3,4 |
| Two questions from the Danish longitudinal Health Behaviour Study | Network and perceived social support – informal: emotional and instrumental | • 0,1,2,3,4 |
| Six questions                                                     | Network and perceived social support – formal : informational               | • 1,2       |
| Demographic and individual characteristics                        |                                                                             |             |
| ISCED                                                             | Education                                                                   | • 0         |
| Five point classification scheme - questionnaire                  | Occupational social class                                                   | • 0         |
| Four questions                                                    | Marital status, cohabiting status, children living in the household         | • 0         |

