For the secondary outcome measure 'Parenting Alliance Measure' it will be tested using the general linear univariate model, whether the mean values differ between the two intervention groups at time 3 (6 months following birth), and time 4 (12 months following birth).

The unadjusted analyses are the primary analyses. If possible all analyses will be repeated adjusted for the protocol specified stratification variable and the baseline value.

Three explorative subgroup analyses may be conducted in each case provided the subgroup interacts significantly with the intervention.

In addition to analyses performed for individuals, descriptive analyses reporting the interdependency within the couple as well as within the specific antenatal education group, and at the facilitator level will be performed by intraclass correlation.

Process evaluation will be conducted with a mixed methods approach using quantitative questionnaire data and qualitative interviews with participants and service providers. We will examine program fidelity, e.g. whether the protocol is followed in program delivery, and how much of the intended program the participants are receiving, as well as program reach e.g. what proportions of the intended groups are participating in the program, as these factors have an impact on the effect of an intervention(33). The incremental societal cost of the intervention will be computed and compared to the measured outcomes in a cost-effectiveness analysis. Direct health care costs and productivity cost in terms of labour market participation and short term absence will be calculated.

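### Smoking, mental well-being and anxiety are first measured at 37 weeks, after all three antenatal sessions, so these explorative outcomes have no pre-intervention value

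*Protocol*

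**What the plan says.** The time points are defined in 6.1 as "baseline i.e. time point 0 (tp0) (<20 weeks gestation), 37 weeks gestation (tp1"), followed by 9 weeks (tp2), 6 months (tp3) and 1 year (tp4) after the expected due date. On the intervention, 3.5 states: "The first intervention session will take place at 25 weeks gestation, followed by 2 sessions at 33 and 35 weeks of gestation".

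The three measures are scheduled as follows.

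- **Smoking.** The list of explorative outcomes in 6.1 has "Smoking - questionnaire data (tp 1, 2"). Table 1 in 6.2 gives the row "Smoking question from the National health interview survey" time points 1, 2, 3 and 4.
- **Mental well-being.** The 6.1 list gives tp1, 2 and 3. The measurement text, under Medicine use, says "It will be measured using the Warwick-Edinburgh mental well-being Scale (WEMWBS) (tp 1,2,3,4"), and Table 1 agrees with that text.
- **Anxiety.** The measurement text has the first ten SCL-25 items: "anxiety score, SCL-anxiety) will be used to measure anxiety (tp 1,2,3"). Table 1 agrees. The 6.1 list has one shared line: "Antenatal and Post-natal depressive symptomatology and anxiety – questionnaire data (tp0,1,2,3").

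On analysis, 7.2 makes the unadjusted analyses primary and adds: "If possible all analyses will be repeated adjusted for the protocol specified stratification variable and the baseline value".

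**The concern.** A baseline web questionnaire already goes to every participant. Other explorative measures are in it: the depression scale (EPDS), the single stress items and relationship satisfaction all have a tp0 value. Parenting stress cannot be asked about before birth, so its absence at tp0 is natural. Smoking, well-being and anxiety can all be asked about before 20 weeks, and the protocol gives no reason for leaving them out.

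Three things are at stake. The comparisons of these outcomes are less precise than they could be. A chance imbalance between the arms in smoking, anxiety or well-being at entry cannot be seen directly. And no change from baseline can be analysed, although 12.3 names a possible PhD project on intervention effects on depression and anxiety. A statistical analysis plan cannot repair this later, because a baseline that was not collected cannot be recovered.

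**Working it through.** The protocol states no figure on this point, so there is none to reproduce. The check sets the schedule entries side by side and then illustrates the loss of precision.

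**Step 1: timing.** tp1 is at 37 weeks (6.1) and the antenatal sessions are at 25, 33 and 35 weeks (3.5). The gaps are 37 − 25 = 12, 37 − 33 = 4 and 37 − 35 = 2 weeks. Every antenatal session precedes the first measurement.

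**Step 2: schedule entries.**

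| Measure | 6.1 list | 6.1 measurement text | Table 1 | tp0 value? |
|---|---|---|---|---|
| Smoking | 1, 2 | none given | 1, 2, 3, 4 | no |
| WEMWBS | 1, 2, 3 | 1, 2, 3, 4 | 1, 2, 3, 4 | no |
| SCL-anxiety | shared line: 0, 1, 2, 3 | 1, 2, 3 | 1, 2, 3 | no |
| EPDS | shared line: 0, 1, 2, 3 | 0, 1, 2 | 0, 1, 2 | yes |
| MDI | shared line: 0, 1, 2, 3 | 3 | 3 | no |

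Smoking is also absent from the tp0 demographic and individual characteristics in 6.1 and Table 1. The table shows a second, smaller point: the later time points of smoking and well-being differ between the 6.1 list and Table 1.

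**Step 3: the shared depression-and-anxiety line.** The union of its instruments is {0, 1, 2} for EPDS, {3} for MDI and {1, 2, 3} for SCL-anxiety, which gives {0, 1, 2, 3}. That is exactly the entry in the list. The breastfeeding line is built the same way: intention {0, 1}, partner support {0, 2}, difficulties {2} and duration {3} also give {0, 1, 2, 3}. The tp0 in the shared line is therefore most naturally the EPDS alone.

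**Step 4: precision, for the two continuous scores only.** In a linear model, adjusting for a baseline value that correlates r with the follow-up value multiplies the residual variance by 1 − r². The protocol gives no r, so a range is assumed.

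| Assumed r | 1 − r² | Variance cut | Equivalent sample size factor 1/(1 − r²) |
|---|---|---|---|
| 0.3 | 0.91 | 9% | 1.10 |
| 0.5 | 0.75 | 25% | 1.33 |
| 0.7 | 0.51 | 49% | 1.96 |

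**Step 5: allowance for covariates already available.** The EPDS, the Perceived Stress Scale and other related measures are collected at tp0. Suppose, for illustration, that they alone bring the variance factor to 0.75, and that adding the score's own baseline brings it to 0.51. The further gain is then 1 − 0.51/0.75 = 1 − 0.68 = 32%, not 49%.

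Smoking is presumably analysed as a status, so the formula in step 4 does not carry over. No figure is given for it.

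**The case against.** Several objections carry weight.

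- **These outcomes are explorative.** 6.1 says so and cites scope and power. They carry no power claim, and randomisation keeps the comparison valid without a baseline. This stands, and it limits the priority of the point.
- **Section 7.2 breaks no promise.** A reader might infer that the plan commits itself to an analysis that it cannot run. The text does not support that: the adjusted repeat is conditional on being possible, the unadjusted analysis is primary, and models are named only for the primary and secondary outcomes. The condition is needed anyway, since epidural use and the postnatal parenting scales have no baseline either.
- **Section 6.1 does not clearly list an anxiety score at baseline.** A reader might take the shared line as a contradiction with Table 1. Step 3 shows a simpler reading, so only a clarification is called for.
- **Related baseline measures exist.** EPDS, perceived stress, the stress items, sense of coherence and self-rated emotional health are all collected at tp0, and randomisation is stratified for vulnerability. For anxiety and well-being these allow an indirect balance check and some adjustment. Smoking has no such near proxy.
- **A power gain cannot be quoted.** It would need an effect size for these outcomes, which the protocol does not give, and a number of women. On the latter, 7.1 has 878 per arm, while the abstract has 2350 in total, or 1175 per arm at 1:1.
- **It is unknown whether quitters can be told from never-smokers.** One might infer that they cannot, but the wording of the survey question is not reproduced, and it may record former smoking.

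Against all this, the absence of a tp0 value for the three measures is not in dispute. Nor is it disputed that the only cost of adding them is questionnaire length.

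**Conclusion.** The point holds as a modest, specific improvement to three explorative outcomes. It is not a bias, and it is not a contradiction in the analysis plan. Smoking, WEMWBS and SCL-anxiety have no pre-intervention value, so baseline adjustment, a direct balance check and analysis of change are unavailable for them. For the two continuous scores the lost precision is a variance reduction of 9% to 49%. This rests on a linear model and an assumed correlation of 0.3 to 0.7, and it shrinks where related tp0 measures are already used as covariates. A correlation between tp0 and 37 weeks need not hold at the later time points, so the figure may differ there. For smoking the loss is chiefly the balance check and interpretability, and it is the clearest of the three because nothing else at tp0 stands in for it.

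**What to change.** Add the smoking question to the tp0 questionnaire. Preferably add the ten SCL anxiety items and the WEMWBS as well. Update the 6.1 list, the 6.1 measurement text and Table 1 to match, and state that these outcomes will be adjusted for their tp0 value. If only one addition is acceptable, it should be the smoking question.

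Two clarifications are needed whichever option is chosen. State that tp0 in the shared depression-and-anxiety line refers to the EPDS, unless SCL-anxiety is added at baseline. Reconcile the later time points between the 6.1 list and Table 1 for smoking (1, 2 against 1, 2, 3, 4) and for well-being (1, 2, 3 against 1, 2, 3, 4).

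The cost is a somewhat longer baseline questionnaire (one question plus, if chosen, two scales) and edits to the text and Table 1. If baseline collection has already closed, make the clarifications and say plainly that these outcomes will be analysed without their own baseline value.
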